### Statistical analysis

The primary and secondary outcomes will be assessed using an intention-to-treat analysis applied to individual participants and repeated using the per-protocol sample (only participants who complete the clinical trial including the second assessment). To compare the effectiveness of ROC with usual care, presenting and best corrected near and distance VA (primary outcome) at the two- and six-month follow-ups will be analyzed and the differences from baseline VA will be used to investigate changes. The near and distance VA change is expected to be normally distributed and analysis of covariance will be used to compare the difference, adjusting for baseline values. Effect sizes for both groups will be calculated using Cohen’s d coefficient [27]. To determine the effectiveness of ROC on secondary outcomes, a Multivariable General Linear Model will be used to compare differences at two and six months from baseline on the IVI-RC, EQ-5D-3L and CSDD. If the EQ-5D-3L data are skewed, a multivariable quantile regression model will be used. Falls data will be compared across intervention and usual care groups at six months using a negative binomial regression if the data are over-dispersed. Changes in mobility will be analyzed using Mann–Whitney U tests. The difference in utilization of distance and near vision glasses and low vision aids between the treatment groups will be compared using the Chi-squared test and the utilization time will be compared using Student’s t-test or non-parametric test if appropriate. A multi-level model with a random intercept parameter will be utilized to account for within cluster correlations. All analyses will be performed using STATA version 15 (StataCorp. 2017. Stata Statistical Software: Release 15. StataCorp LLC, College Station, TX, USA).

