**Methods/design:**

This protocol describes a multicentered, prospective, randomized controlled trial. A total of 395 participants with distance vision < 6/12 (0.30 LogMAR) and/or near vision N8 (1.00 M) or worse will be recruited from 38 urban and rural aged care facilities across Victoria, Australia. Aged care facilities will be randomized (1:1) to one of two parallel groups. Participants in the ROC group will receive a comprehensive and tailored eye care pathway that includes, as necessary, refraction and spectacle provision, cataract surgery, low vision rehabilitation, and/or a referral to an ophthalmologist for funded treatment. Usual care participants will be referred for an evaluation to the eye care service associated with the facility or an eye care provider of their choice. The primary outcome will be presenting near and distance vision assessed at the two- and six-month follow-up visits, post baseline. Secondary outcomes will include vision-specific quality of life, mobility, falls, depression, and eye care utilization at two and six months. An incremental cost-effectiveness analysis will also be undertaken.

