To date, no study has evaluated the impact of providing comprehensive eye care services to individuals with a broad spectrum of ophthalmic conditions and residing in aged care facilities. Therefore, we will implement a prospective, customized, multicentered, and cluster randomized controlled trial (RCT) to evaluate the clinical, person-centered, and cost-effectiveness of a new model of eye care. We will compare the effectiveness of Residential Ocular Care (ROC) with usual care on improving presenting and best corrected near and distance vision (primary outcome) at the two- and six-month follow-up visits. Secondary outcomes will assess the effectiveness of ROC on improving vision-specific QoL, daily functioning, health-related QoL, depressive symptoms, rate of falls, and eye care utilization, compared to the usual care group at the two- and six-month visits, after baseline, and quantify the cost-effectiveness of ROC at six months after baseline.

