#### Low vision rehabilitation

Participants with VA < 6/12 (0.3 LogMAR) not correctable by either refraction or cataract surgery will be eligible for the low vision rehabilitation pathway. An ACO optometrist will undertake an initial comprehensive vision and ophthalmic review and provide low vision aids where appropriate at no cost. The type of low vision aids provided will be determined by the level of VI, the level of magnification required to perform desired tasks and the participant’s ability to use aids of different designs. Detailed demonstration, training, and instruction on aids will be given to the participant. Details of this examination will be forwarded with referral to the nearest Vision Australia center, Australia’s leading provider of blindness and low vision rehabilitation services, where an appointment will be scheduled within eight weeks. At this appointment, a Vision Australia Occupational Therapist will conduct a “Techniques for Daily Living” session with the participant, focusing on areas of difficulty and concern. Each session will be adapted to the individual circumstances of the resident, but be based around application of the following techniques:*Lighting:* general and/or task lighting;*Size:* bring things closer, make them larger, and vary the use of prescribed magnification;*Contrast:* increase the contrast between the foreground and the background;*Senses:* touch, scent, sound, and taste;*Marking:* tactile and/or contrast colored marking;*Labeling:* large print, Braille, or audio labels;*Organization:* different systems for organizing belongings;*Equipment:* everyday devices and/or functional use of low vision aids.

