### Outcomes

#### Distance and near vision (primary)

Distance presenting VA at the two- and six-month follow-up visits after baseline. Participants’ uniocular and binocular distance VA (LogMAR charts) will be assessed, according to established protocols with their current presenting correction.

Uniocular and binocular presenting near VA will be assessed using LogMAR word reading cards, viewed at habitual working distances in the range of 25–40 cm. Reading fluency will be assessed as the time taken to read a block of text (Pepper Visual Skills for Reading Test cards) 0.3 log units larger than threshold. Following refraction, VAs at distance and near and contrast sensitivity will be assessed through best corrected VA.

For distance uniocular and binocular presenting VA, mild-moderate VI will be categorized as VA > 0.3 and ≤ 1.0 log units, while severe VI will be defined as VA > 1.0 log units. The proportion in each category will be compared between groups.

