### Sample size

Pilot data collected from 31 participants residing in a single-site aged care facility were used to guide power calculations for this study ([name], [name], [name], [name]: Vision Optimisation in Residential Care: A pilot study, unpublished, 2011). They showed that following correction, 30% of participants had improved distance vision by at least two lines and 30% of the participants improved by ≥ 0.2 Log units on a text reading chart for near vision. Therefore, the sample size calculation is based on achieving a 30% improvement in VA (near and distance vision) at two- and six-month follow-up visits in the intervention group compared to controls. The anticipated effect size will be ~ 0.65 based on our pilot work. At a significance level of 0.05, with 38 participants in each arm (overall total of 76 participants) we will have 80% power to detect a group difference. We assume an intra-cluster correlation coefficient (ICC) within-facility of 0.05 which corresponds to the levels found in similar work in nursing homes [28]. The inflation factor (or design effect) will be estimated using the following formula: Inflation factor = 1+ (number of patients per facility [50]-1) X ICC = 3.5. To take cluster design into account, we need a total sample size of 266 [76 × 3.5]. However, to adjust for non-compliance with the intervention (~ 10% due to people who seek vision care on their own in the usual care arm, or people who refuse the intervention in the intervention arm) and loss to follow-up (~ 25% largely due to deaths), the effective sample size needs to be increased by a factor of 1.48 (1/0.90 × 1/0.75) resulting in an initial enrolment requirement of 395 individuals.

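### The primary outcome is defined inconsistently: four comparisons in the abstract, eight in the aims and analysis, with one 0.05 and no success rule

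*Protocol article*

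**What the plan says.** Five places in the protocol article bear on the primary outcome.

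- **Abstract, Methods/design:** "The primary outcome will be presenting near and distance vision assessed at the two- and six-month follow-up visits, post baseline". Best-corrected acuity is not mentioned.
- **Background, closing paragraph (aims):** ROC is to be compared with usual care on "improving presenting and best corrected near and distance vision (primary outcome) at the two- and six-month follow-up visits".
- **Statistical analysis:** "presenting and best corrected near and distance VA (primary outcome) at the two- and six-month follow-ups will be analyzed", using analysis of covariance on change from baseline.
- **Outcomes, Distance and near vision (primary):** the text opens with "Distance presenting VA at the two- and six-month follow-up visits after baseline". Near acuity, reading fluency and best-corrected acuity follow under the same heading. For presenting acuity, "uniocular and binocular distance VA (LogMAR charts) will be assessed", and near acuity is likewise taken with each eye and with both. Neither is named as the analysis eye. The section then defines categories of distance impairment and adds: "The proportion in each category will be compared between groups".
- **Sample size:** the target is a 30% improvement in near and distance acuity at both visits, derived from pilot responder rates. It is converted to a standardised effect of about 0.65: "At a significance level of 0.05, with 38 participants in each arm", for 80% power.

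No section ranks the measures or visits, divides the 0.05, or says whether one success or all of them are needed.

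**The concern.** Whether best-corrected acuity is primary has two different answers in the same document. This is a contradiction in stated text, not detail left out for brevity. With several candidate measures, two visits and no success rule, the comparison that carries the trial's conclusion could be chosen after the results are known. The single 0.05 and the 80% power each describe one comparison. Neither describes the trial's conclusion once four or eight comparisons share the primary label.

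Best-corrected acuity also fits one part of the intervention poorly. It is measured after refraction, so it does not depend on whether a participant owns or wears the right spectacles. A resident whose only need is new glasses can gain a great deal in presenting acuity and nothing in best-corrected acuity. The more residents there are on the spectacle pathway, the more the effect on that endpoint is diluted.

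**Working it through.** **Reproducing the plan's figure.** Inputs from Sample size: effect 0.65 SD, 0.05 (taken as two-sided), 80% power.

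- n per arm = 2 × ((1.960 + 0.842)/0.65)² = 37.2, rounded up to 38, or 76 in total. A one-sided test would need 30, so the plan's figure is two-sided.
- 76 × 3.5 = 266.
- 266/(0.90 × 0.75) = 394.07, rounded up to 395.

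The stated numbers reproduce as the size for one comparison.

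**Counting the primary comparisons.**

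- Aims and Statistical analysis: 2 (presenting, best-corrected) × 2 (near, distance) × 2 (two, six months) = 8.
- Abstract: 2 (near, distance) × 2 visits = 4.

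The choice of eye and the category comparison are left out of both counts.

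**If any one success at 0.05 is enough.** For independent tests the chance of at least one false positive is 1 − 0.95^k. For correlated tests it was simulated with equally correlated normal test statistics. The documents give no correlation, so these values are assumed.

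| Tests | Independent | Correlation 0.5 | Correlation 0.8 |
|---|---|---|---|
| 4 | 18.5% | 16% | 11% |
| 8 | 33.7% | 25% | 16% |

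Even at a correlation of 0.9, eight tests give about 12%.

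**If all must succeed.** There is no inflation of false positives, but with 80% power per test and independence the joint power is 0.8^8 = 17% for eight and 0.8^4 = 41% for four. Positive correlation raises these figures.

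**Cost of splitting 0.05 over two endpoints.** The first Holm step is at 0.025. Detectable effect = (critical value at α/2 + quantile at 0.80) × 2/√(effective N). With normal quantiles the ratio is (2.241 + 0.842)/(1.960 + 0.842) = 1.10, a rise of about 10%. The absolute values depend on the design effect.

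- *Cluster size implied by the enrolment:* 395 × 0.75 = 296, over 38 facilities is 7.8 each. Design effect = 1 + 6.8 × 0.05 = 1.34, so effective N = 221. With t quantiles on 36 degrees of freedom (38 facilities − 2), the detectable effect goes from about 0.39 to 0.43 SD.
- *The protocol's design effect of 3.5:* 296/3.5 = 85. The detectable effect goes from 0.61 (normal) or 0.63 (t) to 0.67 or 0.69 SD, slightly above the planned 0.65.

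Neither line takes off the 10% for non-compliance.

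**Enrolment by the protocol's own method if the 0.05 is divided equally.**

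| Primary tests | Level each | Per arm | Total × 3.5 | Enrolled |
|---|---|---|---|---|
| 1 | 0.05 | 38 | 266 | 395 |
| 2 | 0.025 | 45 | 315 | 467 |
| 4 | 0.0125 | 53 | 371 | 550 |
| 8 | 0.00625 | 61 | 427 | 633 |

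**The case against.** The strongest reply is that a multiplicity rule is commonly left to the analysis plan, which is not shown. The value 0.05 appears only in Sample size. Nothing says that each comparison is tested at that level or that one success suffices. This stands as far as it goes: the 34%, 25% and 16% are conditional on an unwritten rule and, for the last two, on assumed correlations. They do not show that the trial's error rate is inflated. But an analysis plan could not make the abstract agree with the aims and Statistical analysis on best-corrected acuity.

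Some stronger readings are tempting but not supported:

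- *Three rival definitions.* The Outcomes text opens with distance acuity alone, but its heading covers distance and near, and its next paragraph adds near and best-corrected acuity. Read whole, it agrees with the aims. The clear conflict is between the abstract and the body.
- *Twenty-four tests, counting right, left and both eyes.* The one-eye and two-eye wording attaches to presenting acuity only, so multiplying all eight by three has no basis.
- *Best-corrected acuity lies beyond the reach of ROC, or of its main component.* The Intervention section lists four options without ranking them. Cataract surgery and ophthalmic treatment can change best-corrected acuity.
- *The pilot effect was in presenting acuity.* Sample size says only that vision improved after correction. That could mean supplied glasses or the best refraction.
- *The two-month visit comes too early for low vision rehabilitation.* The wording "where an appointment will be scheduled within eight weeks" concerns a daily-living session. Nothing says that session changes chart acuity, and aids are given at the optometrist's initial review.

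**Conclusion.** The concern holds in this limited form. The abstract gives four primary comparisons, and the aims and Statistical analysis give eight. The eye, the decisive visit and the success rule are all open, and the sample size fits only one comparison. The consequence depends on a rule that the document does not state: up to 34% false-positive risk if any one result counts (11 to 19% for the abstract's four, over correlations from 0.8 down to 0), or joint power as low as 17% if all eight are required. The second figure assumes independence and 80% power per test. Best-corrected acuity is a diluted endpoint for residents who need only spectacles, not an irrelevant one. Because the primary outcome decides what the trial concludes, this should be settled before anyone sees unblinded results.

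**What to change.** Adopt one definition, built on the presenting vision that the abstract already names. Use it in the abstract, Background aims, Outcomes, Statistical analysis and Sample size. Name the eye, the visit and the success rule. One workable choice is binocular presenting acuity at six months, in either of two forms:

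- **One measure** (distance or near), tested at two-sided 0.05; or
- **Distance and near**, tested with Holm at an overall two-sided 0.05, with effectiveness claimed only for the measure or measures that pass.

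Move best-corrected acuity, one-eye acuity, the other visit and the impairment categories to secondary outcomes. Restate the sample-size target on the chosen endpoint instead of as a 30% improvement at both visits. Binocular, six months and Holm are options; what matters is that one choice is fixed.

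**Cost.** No new data are needed. It is more than a wording change, though. The Trial status section expects recruitment to finish on 1 December 2018, so demoting stated primary outcomes needs a dated, disclosed amendment. It should go to the ethics committees and the registry, as Ethics and dissemination requires, before unblinded data are seen. A single measure leaves 38 per arm and 395 enrolled as they are. With two measures, the roughly 10% rise in detectable effect is comfortable only if the smaller design effect is accepted. Under the protocol's own 3.5 it slightly exceeds the planned 0.65, and the protocol's method would call for 467 enrolled.

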### Settings and study participants

Prospective participants will be recruited from 38 aged care facilities in urban and rural Victoria, Australia. Before enrolment or study assessments being performed, prospective participants will be asked to sign a written consent form. Residential care staff will identify participants who are cognitively able to give informed consent. Participants who consent to participate in the study will be screened for study eligibility by a research assistant.

The inclusion criteria are:Presenting distance < 6/12 (0.30; Logarithm of the Minimum Angle of Resolution-LogMAR) and/or near vision ≤ N8 (1.00 M) assessed uniocularly and binocularly using the Bailey-Lovie LogMAR [16] charts;Able to speak English;Moderate cognitive functioning or better as assessed by the Psychogeriatric Assessment Scale (PAS) [17] (score ≤ 15);Ability to undergo VA testing and provide reliable results.

The exclusion criteria are:Residents in respite care (short-term stay);Severe cognitive impairment (score of ≥ 16 on the PAS);Non-English speaking;Inability to be tested for vision;Contraindication(s) as indicated by the general practitioner responsible for the resident’s care.

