### Randomization

An independent statistician will perform the randomization sequence generation using a computer-generated list. For logistical reasons and to minimize confounding effects, stratified cluster randomization designs will be used to randomize participants by residential aged care facility (stratified by size and region) to the intervention (ROC) or control (usual care) arm. Participants in the same aged care facility will all be assigned to the same study arm. The allocation sequence will be concealed from the research assistants enrolling and assessing participants. Residential care facility staff, the research study coordinator, and the eye health professionals delivering ROC will not be masked to the group allocation as this is impractical.

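### Facilities are randomised within strata of size and region, but the primary acuity model names only baseline values as covariates and no analysis names the strata; if the strata are prognostic, the test is mildly conservative

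*Protocol article*

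**What the plan says.** Under Randomization, the protocol article states that "stratified cluster randomization designs will be used to randomize participants by residential aged care facility (stratified by size and region". The Abstract gives the ratio and the unit: "Aged care facilities will be randomized (1:1) to one of two parallel groups". Settings and study participants gives the number of clusters, 38 facilities.

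Under Statistical analysis, the primary outcome is change in near and distance acuity, for which "analysis of covariance will be used to compare the difference, adjusting for baseline values". For the secondary scales, "a Multivariable General Linear Model will be used to compare differences at two and six months from baseline on the IVI-RC, EQ-5D-3L and CSDD", with a multivariable quantile regression as the fallback if EQ-5D-3L is skewed. The covariates of these two models are not named. Changes in mobility are compared with a Mann–Whitney U test. Clustering is covered by one general sentence: "A multi-level model with a random intercept parameter will be utilized to account for within cluster correlations".

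Neither size nor region is named as a covariate in any analysis in the article.

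**The concern.** The analysis should respect the restrictions placed on the randomisation. Stratifying by size and region keeps the arms similar on those factors, so differences between strata add little to the true sampling variation of the treatment effect. A model without the strata still counts those differences as error.

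The random intercept does not correct this. It models correlation among residents of one facility, but stratum differences remain in the between-facility variance that sets the standard error of a facility-level comparison.

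At stake are intervals wider than they need be and a test whose true size falls below the stated 5%. The direction is conservative: there is no bias and no excess of false positives.

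**Working it through.** **The plan's own figure.** Sample size uses a standardised effect of 0.65, alpha 0.05 (two-sided reproduces it), 80% power, an ICC of 0.05, a design effect stated as 3.5, 10% non-compliance and 25% loss.
- 38 per arm, 76 in total (power 80.9%).
- 76 × 3.5 = 266.
- 266 / (0.90 × 0.75) = 394.07, rounded up to 395. The stated 395 reproduces.

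**Inputs for this check.**
- ICC 0.05 (Sample size).
- 395 enrolled in 38 facilities with 25% loss: 395 × 0.75 = 296 completers, and 296 / 38 = 7.8 per facility (call this m).
- R², the share of between-facility variance in acuity change explained by size and region given baseline acuity. The article does not give it, so a range of 0 to 75% is assumed.

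**Formula.** With total variance set to 1, the variance of a facility mean is ICC + (1 − ICC)/m as the model without strata sees it, and (1 − R²) × ICC + (1 − ICC)/m as the stratified design delivers it. The ratio of model SE to true SE is the square root of the first over the second. The true size of a nominal 5% test is 2 × [1 − Φ(1.96 × ratio)].

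Without strata: 0.05 + 0.95/7.8 = 0.172. For example, at R² = 50%: 0.025 + 0.95/7.8 = 0.147, so the ratio is √(0.172/0.147) = 1.08.

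| Assumed R² | SE ratio | True size of 5% test |
|---|---|---|
| 0% | 1.00 | 5.0% |
| 10% | 1.02 | 4.7% |
| 25% | 1.04 | 4.2% |
| 50% | 1.08 | 3.4% |
| 75% | 1.13 | 2.7% |

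With no loss to follow-up (395/38 = 10.4 per facility), the ratio runs from 1.00 to 1.17 over the same range.

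**Simulation check.** Facility means were simulated for 38 facilities in four assumed strata, allocated 1:1 within stratum, with 20,000 runs per setting. At 7.8 per facility and R² of 0, 25, 50 and 75%:
- Strata left out: ratio of mean model SE to empirical SE 0.99, 1.04, 1.08 and 1.14; size 5.1, 4.0, 3.6 and 2.6%.
- Strata included: size 5.2, 4.7, 5.1 and 4.8%.

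**Primary power.** At 7.8 per facility the design effect is 1 + 6.8 × 0.05 = 1.34, so 296 completers are worth about 296/1.34 = 221 independent ones, against 76 required. With 19 facilities per arm, the SE of the difference is √(2 × 0.172/19) = 0.1345.
- Effect 0.65: 0.65/0.1345 = 4.83. Against a 36-df critical value of 2.03, power without strata is about 99.7%.
- Effect diluted by 10% for non-compliance (0.585): 0.585/0.1345 = 4.35, power about 99%.
- Adding the strata raises power by less than 0.3 percentage points at every R² from 0 to 75%.

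**The case against.** The strongest reply is that an article condenses the full plan and that covariate lists usually sit in a statistical analysis plan, which is not shown. That carries weight for the secondary scales. It carries less for the primary outcome, because the article does not stay silent there: it names what the ANCOVA adjusts for, and the strata are not in it.

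Several stronger readings are tempting and do not stand.

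- **That every model adjusts for baseline alone.** The secondary models are called multivariable with covariates unnamed; baseline values and strata may be among them. An analysis of change without baseline would have more residual variance than ANCOVA: the ratio of ANCOVA to change-score variance is (1 + r)/2, so ANCOVA is 25% lower at r = 0.5 and 15% lower at r = 0.7 (assumed correlations). But the article does not fix such an analysis, so this is a reason to name the covariates and not a demonstrated error.
- **That the standard errors are certainly too large.** If size and region do not predict acuity change given baseline, the standard error is correct. The article gives no figure either way.
- **That the primary comparison loses material power.** Starting from exactly 80%, an SE ratio of 1.17 would bring power down to 70%. The article's own ICC, effect and enrolment imply about 99%, so that starting point does not apply. For the secondary outcomes no effect size is stated, so nothing can be said about their power.
- **That false positives are inflated.** The departure from 5% is downward.
- **That mobility needs baseline in its model.** It is compared with a rank test, so this would mean a different method and not an added covariate.

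**Conclusion.** The point holds for the primary acuity analysis. The design stratifies by size and region, and the stated adjustment leaves both out. The cost is a standard error 0 to 13% too large and a true size of 5.0 to 2.7% for a nominal 5% test, with no bias and a negligible effect on primary power.

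These figures rest on the article's ICC of 0.05, on equal facilities of 7.8 completers, on the random intercept being applied to the primary ANCOVA, and on the assumed 0 to 75% of between-facility variance explained. The size is therefore modest and possibly nil. For IVI-RC, EQ-5D-3L and CSDD the covariates are simply not named. Naming the strata is a free improvement that matches the analysis to the randomisation; it does not rescue an invalid test.

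**What to change.** In Statistical analysis, state that the primary mixed model for acuity includes facility size stratum and region as fixed effects, alongside baseline acuity and the facility random intercept. State also that the multivariable models for IVI-RC, EQ-5D-3L and CSDD include the same strata and the outcome's own baseline value.

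The cost is a sentence or two, settled before the data are analysed. Size and region must be known for each facility in order to randomise, and the baseline values are already needed to calculate change, so no further data, visits or participants are required.

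### The Mann–Whitney test on mobility change cannot adjust for baseline or carry the facility random intercept, and the models for IVI-RC, EQ-5D-3L and CSDD do not say whether baseline is a covariate

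*Protocol article*

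**What the plan says.** All four analyses are set out in one paragraph of the Protocol article, under Statistical analysis.

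- **Acuity (primary):** the change from baseline is compared, and "analysis of covariance will be used to compare the difference, adjusting for baseline values".
- **IVI-RC, EQ-5D-3L, CSDD:** "a Multivariable General Linear Model will be used to compare differences at two and six months from baseline on the IVI-RC, EQ-5D-3L and CSDD". There is a fallback for one of them: "If the EQ-5D-3L data are skewed, a multivariable quantile regression model will be used". Neither sentence names a covariate.
- **Mobility (ACFI):** "Changes in mobility will be analyzed using Mann–Whitney U tests".
- **Clustering, as a closing sentence:** "A multi-level model with a random intercept parameter will be utilized to account for within cluster correlations".

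On the design, "Prospective participants will be recruited from 38 aged care facilities in urban and rural Victoria, Australia", and "Aged care facilities will be randomized (1:1) to one of two parallel groups" (Abstract). The Randomization section stratifies facilities by size and region only. Under Person-centered outcomes, the mobility comparison is described as one of group means, which is not what a Mann–Whitney test compares.

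**The concern.** Subtracting the baseline is not the same as adjusting for it. When ρ is below 1, a change score over-corrects: the arm that happens to start worse tends to appear to improve more. An ordinal mobility score adds to this, because residents at either end of the scale can move in one direction only.

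For mobility the choice of test settles the matter. A Mann–Whitney test on change has no place for a baseline covariate, so no later covariate list could supply one without replacing the test. In its usual form it also treats residents as independent, so the random-intercept sentence cannot apply to it.

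For the other three outcomes the doubt comes from contrast: baseline adjustment is written out for acuity and not for them. Together these four outcomes carry most of the trial's person-centered conclusion, and EQ-5D-3L also supplies the effect term of the cost-effectiveness ratio. Nothing in the randomization balances their baseline values beyond chance across 38 facilities.

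**Working it through.** **1. The plan's own figures.** Sample size section: effect size 0.65, significance level 0.05 (taken as two-sided), 80% power.

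- Per arm: 2 × (1.96 + 0.842)² / 0.65² = 37.2, so 38 per arm and 76 in total. This reproduces.
- 76 × 3.5 = 266. This reproduces.
- 266 / (0.90 × 0.75) = 394.1, against 395 stated. This agrees within rounding.

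These figures concern acuity. The protocol states no power for any secondary outcome, so they neither support nor weaken the point.

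**2. Variance of a change score relative to ANCOVA.** Assume equal SD at baseline and follow-up, and the same ρ between and within facilities. In units of SD²:

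- Var(change) = 2(1 − ρ)
- Var(ANCOVA) = 1 − ρ²
- Ratio = 2 / (1 + ρ)

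The protocol gives no ρ, so a range is shown. The last column assumes that the baseline-adjusted analysis would have 80% power: Φ(2.802/√ratio − 1.96).

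| ρ (assumed) | Var(change) / Var(ANCOVA) | Power of unadjusted change |
|---|---|---|
| 0.3 | 1.40/0.91 = 1.54 | 62% |
| 0.5 | 1.00/0.75 = 1.33 | 68% |
| 0.7 | 0.60/0.51 = 1.18 | 73% |
| 0.8 | 0.40/0.36 = 1.11 | 76% |
| 0.9 | 0.20/0.19 = 1.05 | 78% |

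These are linear-scale results. For a rank test on an ordinal score they indicate direction and rough size only. A power figure specific to mobility would need the number and distribution of ACFI mobility levels, which the protocol does not give.

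**3. Size of a chance baseline difference.** Inputs: 395 participants, 38 facilities, 1:1 allocation, ICC 0.05 (the plan's value, assumed here to apply to these scores too).

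- All enrolled: 395/38 = 10.4 per facility; design effect 1 + 9.4 × 0.05 = 1.47; SE = √(2 × 1.47/197.5) = 0.12 SD.
- After 25% loss: 395 × 0.75 = 296, or 7.8 per facility; design effect 1 + 6.8 × 0.05 = 1.34; SE = √(2 × 1.34/148) = 0.13 SD.

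**4. What passes into the effect.** If one arm starts higher by δ, its change is lower by (1 − ρ)δ. For a 1-SE difference of 0.13 SD:

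- ρ 0.5: 0.5 × 0.13 = about 0.07 SD. The change-score effect has its own SE of √(2 × 0.5) × 0.13 = 0.13 SD.
- ρ 0.7: 0.3 × 0.13 = about 0.04 SD, against √(2 × 0.3) × 0.13 = 0.10 SD.

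**5. Does comparing differences from baseline rule out adjustment?** No. With arm T, baseline Y0 and follow-up Y1, the model Y1 − Y0 = a + bT + cY0 is the same as Y1 = a + bT + (1 + c)Y0, so the effect b is identical. The acuity sentence shows the plan using exactly this form: a change from baseline, adjusted for baseline. The wording for IVI-RC, EQ-5D-3L and CSDD is therefore compatible with either analysis.

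**The case against.** A reader might infer that all four secondary outcomes are compared as unadjusted changes and that power is lost on all of them. The protocol does not support this for IVI-RC, EQ-5D-3L and CSDD. Their models, including the quantile-regression fallback, are called multivariable, which implies covariates beyond arm. Baseline is neither listed nor excluded, and step 5 shows that a change outcome does not exclude it. Covariate lists for secondary models are commonly left to a statistical analysis plan, and none is shown. This objection stands: for these three the point is a request to state what is intended.

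A reader might also infer bias. Under randomization by facility the change-score comparison is unbiased on average, and chance imbalance is already part of its sampling variance. With clustering handled correctly, the type I error would stay nominal. This stands too: the harm is lost precision, plus an error conditional on the imbalance that happens to occur. By step 4 that error is smaller than the standard error of the effect itself.

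Finally, ρ and the 80% anchor are assumptions, and at ρ 0.9 the loss is only 2 power points. That limits the size of the point but does not remove it for mobility, where the named test cannot adjust at any ρ and cannot take the random intercept either.

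**Conclusion.** The point holds firmly for mobility and conditionally for the other three outcomes.

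For mobility, the named test contradicts the plan's own statement on clustering and gives up the baseline adjustment used for acuity. On a linear scale an unadjusted change has 1.33 times the ANCOVA variance at ρ 0.5 and 1.11 times at ρ 0.8, and it carries (1 − ρ) of any baseline difference into the comparison with reversed sign. These figures rest on equal variances, an assumed ρ, and a linear approximation to a rank test.

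For IVI-RC, EQ-5D-3L and CSDD the same loss arises only if baseline is in fact left out. The text does not say that it is, so no error is shown there.

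The outcomes are secondary and the primary acuity analysis is unaffected. The change is still worth making, because it costs almost nothing.

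**What to change.** In the Statistical analysis section:

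1. Replace the Mann–Whitney test with a model of follow-up ACFI mobility, ordinal or linear, with baseline ACFI mobility as a covariate and a facility random intercept. Align the mobility sentence under Person-centered outcomes with it.
2. For IVI-RC, EQ-5D-3L and CSDD, state that each outcome's own baseline score is a covariate in the random-intercept model, and in any quantile-regression fallback for EQ-5D-3L. If this is already intended, the sentence only confirms it; if not, it is a gain in precision at no cost in data.

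The baseline scores are already needed to form the changes, so no new data, visits or participants are required. The cost is one extra parameter per model and, for mobility, a modelling assumption (such as proportional odds or linearity) in place of a rank test.
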